## Abstract

Ischemic stroke (IS) is characterized by high morbidity and high mortality. The integration of Traditional Chinese medicine (TCM) and western medicine has shown promising benefits in relieving symptoms, promoting neurological recovery, and improving the quality of life of patients with IS. In TCM, *Qi*-deficiency along with blood-stasis (QDBS) syndrome is one of the common types of IS that is treated by invigorating *Qi* and activating blood circulation. In TCM theory, improving the corresponding degree of prescription–syndrome correlation (PSC) is helpful to improve clinical efficacy. In this study, we intend to use similar prescriptions that invigorate *Qi* and activate blood circulation: *Buyang Huanwu* granules (BHG), *Naoxintong* capsules (NXTC), and *Yangyin Tongnao* granules (YTG). The goal is to evaluate their level of PSC inpatients with IS with QDBS syndrome and find relevant biomarkers to provide an objective basis for precise treatment of TCM and improve the clinical therapeutic effects. A multicenter, randomized, double-blinded, and placebo-controlled intervention trial will be conducted in IS patients with QDBS syndrome, followed by an add-on of Chinese patent medicine. A total of 160 subjects will be randomly assigned to the BHG, NXTC, YTG, and placebo groups in a 1:2:1:1 allocation ratio. All subjects will undergo 28 days of treatment and then followed for another 180 days. The primary outcome is the changes in the National Institutes of Health Stroke Scale score after 28 days of medication. The secondary outcomes include the modified Rankin scale score, activity of daily living scale score, and TCM symptom score. Data will be analyzed in accordance with a predefined statistical analysis plan. Ethical approval of this trial has been granted by the Research Ethics Committee of the First Affiliated Hospital of Zhejiang Chinese Medical University (ID: 2017-Y-004-02). Written informed consent of patients will be required. This trial is registered in the Chinese Clinical Trial Registry (ChiCTR1800015189), and the results will be disseminated to the public through peer-reviewed journals and academic conferences.

## Introduction

Stroke is the second leading cause of death and a leading cause of disability worldwide (Feigin et al., 2014; Norberto et al., 2017). Ischemic stroke (IS) is the most common type and occurs after thrombosis in the brain or neck blood vessels (Fukui et al., 2017). From 1990 to 2010, the absolute number of first-ever IS patients increased by 37%, mortality increased by 21%, and the loss of disability-adjusted life-years increased by 18% in low- and middle-income countries (Feigin et al., 2014). One of the most important therapeutic strategies for IS is to promote neurological function recovery, and therefore, it is of great practical significance to search for therapeutic targets and drugs to improve neurological function in the later stages of IS. Traditional Chinese medicine (TCM) is a unique and complex medical system that developed over thousands of years and is widely used in Asia as a supplement therapy to western medicine in treating IS. The integration of TCM and western medicine has shown a promising benefit in relieving symptoms, promoting neurological recovery, and improving the quality of life of patients with IS (Wu et al., 2007; Chen et al., 2013; Zhang et al., 2013).

The concept of TCM syndromes (*zheng* in Chinese) reflects inherent pathological variations in the clinic; this important component of TCM theory contributes to identifying human body patterns and guides TCM treatments with herbs (Zhou et al., 2019). In TCM, “prescription–syndrome correlation” (PSC) refers to the high correlation between the compatibility of herbal medicines in a prescription and the disease mechanism that the prescription is directed against (Xin et al., 2010). Since the therapeutic effect is the sole criterion to judge the PSC, improving the corresponding degree of the PSC is the key way to enhance clinical efficacy and also the goal of TCM clinical practice and basic research (Lu et al., 2014). At present, the evaluation of clinical efficacy after TCM treatment is mainly based on improvement of the patients’ syndromes (symptoms, tongue, and pulse). However, due to the subjectivity and fuzziness of the syndrome concept, it is difficult to objectively evaluate the prescription, syndrome, and curative effect. For this reason, we will combine subjective symptoms with objective modern medical diagnosis indicators to objectively clarify the degree of correlation between prescription and syndrome.

*Qi*-deficiency with blood-stasis (QDBS) syndrome is a common type of IS addressed in TCM. Hemiplegia, hypoesthesia, white complexion, shortness of breath, fatigue, spontaneous sweating, dull dark and greasy or bitten tongue, and weak or irregular pulse are usually observed in patients with QDBS. Invigorating *Qi* and activating blood circulation (*Yiqi Huoxue* in Chinese) is the most effective IS treatment in TCM, and its corresponding representative prescription is *Buyang Huanwu* decoction (BHD) proposed by *Wang Qing-ren* in the *Qing* dynasty. BHD has been used to treat IS with QDBS syndrome for nearly 200 years, and it is now used as a basic prescription to treat QDBS in IS. A large number of studies have been carried out to assess the clinical efficacy, underlying mechanisms, and drug substance basis of BHD (Qu et al., 2014; Pan et al., 2017; Ma et al., 2018; Zhang et al., 2018). However, based on the theories of PSC, due to a weak ability of BHD in dredging collaterals, *Naoxintong* capsules (NXTC) was proposed as a supplement to BHD. NXTC is a prescription to invigorate *Qi*, activate blood circulation, ameliorate stasis, and enhance collateral dredging (‘Chinese Experts Consensus on Clinical Application of Naoxintong Capsule’ compilation team, 2017).

Based on previous clinical and basic studies and the theories of *Qi-Yin* related in TCM, overuse or long-term use of BHD may cause *Yin* injury and bleeding (Wan et al., 2015; Wang, 2018). Moreover, purely invigorating *Qi* and promoting blood circulation ignores the elderly pathogenesis of *Yin* deficiency on the treatment of IS with QDBS syndrome (Wan et al., 2015). Thus, *Yangyin Tongnao* granules (YTG) were developed as a prescription for nourishing *Yin*, invigorating *Qi*, and activating blood circulation.

In this study, we will use similar prescriptions for invigorating *Qi* and activating blood circulation (BHD, NXTC, and YTG; compositions listed in **Table 1**) to carry out clinical and biological research on PSC. We will evaluate the level of PSC for *Buyang Huanwu* granules (BHG), NXTC, and YTG in IS with QDBS syndrome, identify helpful clinical biomarkers that are related to IS with QDBS syndrome, and provide an objective basis for precise TCM treatment that can improve clinical therapeutic effect in patients with IS.

**Table 1 T1:** Components of three prescriptions.

Prescription	*YiQi* herbs	*Huoxue* herbs	*Tongluo* herbs	*YangYin* herbs
**BHG**	*Astragalus mongholicus* Bunge (Radix Astragali)	*Angelica sinensis* (Oliv.) Diels (Angelicae Sinensis Radix), *Paeonia lactiflora* Pall. (Paeoniae Radix Rubra), *Oligochaeta*, Lumbricidae (Lumbricus rubellus), *Ligusticum chuanxiong* Hort. (Chuan xiong Rhizoma), *Carthamus tinctorius* L. (Carthami Flos), *Prunus persica* (L.) Batsch (Semen Persicae)	/	/
**NXTC**	*Astragalus mongholicus* Bunge (Radix Astragali)	*Angelica sinensis* (Oliv.) Diels (Angelicae Sinensis Radix), *Paeonia lactiflora* Pall. (Paeoniae Radix Rubra), *Ligusticum chuanxiong* Hort. (Chuanxiong Rhizoma), *Prunus persica* (L.) Batsch (Semen Persicae), *Carthamus tinctorius* L. (Carthami Flos), *Oligochaeta*, Lumbricidae (Lumbricus rubellus), *Hirudo nipponia* Whitman (Whitmania pigra Whitman), *Boswellia carterii* Birdw., (Boswellia carterii), *Commiphora myrrha Engl.*, (Myrrha), *Salvia miltiorrhiza* Bge. (Salviae Miltiorrhizae Radix Et Rhizoma)	*Achyranthes bidentata* Blume (Achyranthes), *Cinnamomum cassia* (L.) J. Presl (Cassia Twig), *Morus alba* L. (Mulberry Twig), *Spatholobus suberectus* Dunn (Caulis Spatholobi), *Buthus martensii* Karsch (Scorpion)	/
**YTG**	*Astragalus mongholicus* Bunge (Radix Astragali)	*Ligusticum chuanxiong* Hort. (Chuanxiong Rhizoma), *Hirudo nipponia* Whitman (Whitmania pigra Whitman)	/	*Dendrobium nobile* Lindl. (Dendrobium candidum), *Rehmannia glutinosa* (Gaertn.) DC. (Radix Rehmanniae), *Pueraria montana* var. lobata (Willd.) (Puerariae lobatae radix)

## Methods and Design

### Trial Design

This trial will be a multicenter, randomized, double-blinded, placebo-controlled intervention study of IS with QDBS syndrome, followed by an add-on of Chinese patent medicine. It is designed to evaluate the efficacy and safety of BHG, NXTC, and YTG for treating IS with QDBS syndrome. The patients will be randomly allocated to four parallel treatment groups using a 1:2:1:1 ratio.

This trial is registered in the Chinese Clinical Trial Registry (No. ChiCTR1800015189) and is in full compliance with the principles of the Declaration of Helsinki and Good Clinical Practice (GCP) guidelines. The protocol has been designed according to the following Standard Protocol Items: Recommendations for Interventional Trials (SPIRIT) checklist and the Recommendations for Interventional Trials and 2013 statement for herbal interventions (Chan et al., 2013a; Huang et al., 2019). We will rigorously follow the latest Consolidated Standards of Reporting Trials (CONSORT 2017) for Chinese herbal medicine recommendations (Cheng et al., 2017). The multicenter clinical trial will be conducted at seven hospitals in China (**Table 2**), and a total of 160 participants will be recruited. After the participants have provided informed consent, they will be enrolled in the trial, which consists of a 28-day treatment period and a 180-day follow-up period. The schematic diagram of study procedures is illustrated in **Figure 1**.

**Table 2 T2:** Hospitals participating in this trial.

Code	Participating hospitals
01	Neurology Department, First Affiliated Hospital of Zhejiang Chinese Medical University
02	Neurology Department, Second Affiliated Hospital of Zhejiang Chinese Medical University
03	Encephalopathy Clinic, Hangzhou Xiaoshan District Hospital of Traditional Chinese Medicine
04	Neurology Department, Huai’an Second People’s Hospital
05	Neurology Department, Third People’s Hospital of Huzhou
06	Encephalopathy Clinic, Luohe Hospital of Chinese Medicine
07	Encephalopathy Clinic, Jinzhou Hospital of Chinese Medicine

**Figure 1 f1:**
[figure not shown]
Flow chart of the study design.

### Ethics and Dissemination

The research team will protect the participants’ rights and safety by adherence to the Declaration of Helsinki, institutional policies and the International Conference on Harmonization-Good Clinical Practice (ICH-GCP). The study was approved by the Research Ethics Committee of the First Affiliated Hospital of Zhejiang Chinese Medical University (ID: 2017-Y-004-02). Eligible participants wishing to participate will be required to sign a written informed consent form. All information collected will be kept strictly confidential. Results of this randomized controlled trial (RCT) will be disseminated to the public through peer-reviewed journals and presentations at local, national, and international academic conferences.

### Diagnostic Criteria of IS

The western medicine diagnostic criteria of IS will refer to the ‘Guidelines for the diagnosis and treatment of acute ischemic stroke in China’ (2014 edition) (Chinese Medical Association, 2015) and the ‘Guidelines for the Treatment of Cerebro-vascular Diseases in China’ (2010 edition) (Chinese Medical Association, 2010). The Chinese medicine diagnostic criteria of IS will refer to the ‘Guiding Principles for Clinical Study of New Chinese Medicines’ (Ministry of Health of the People’s Republic of China, 2002).

### Diagnostic Criteria of TCM Syndrome

The diagnostic criteria of QDBS syndrome in TCM will refer to the ‘Guiding Principles for Clinical Study of New Chinese Medicines’ (Ministry of Health of the People’s Republic of China, 2002) and ‘Syndrome Element Differentiation’ (Zhu, 2008). Syndrome elements are the smallest diagnostic unit for the diagnosis of TCM syndromes (Wang et al., 2012). QDBS syndrome is the combination of “*Qi* deficiency,” “blood stasis,” and “mind” syndrome elements. TCM syndromes of each participant will be blindly evaluated by two Chinese medicine experts (Huang et al., 2019). Consistency will be checked with the kappa test.

### Inclusion Criteria

Patients will be recruited for this study if they meet all of the following criteria: (1) 40 ≤ age ≤ 80 years, (2) consistent with the western and Chinese medicine diagnostic criteria of IS, (3) meet the diagnostic criteria of TCM symptom differentiation (QDBS syndrome), (4) imaging (computed tomography or magnetic resonance imaging) confirmed anterior circulation infarction (Oxfordshire Community Stroke Project clinical classification of complete or partial anterior circulation infarction), (5) course of disease of 1–4 weeks, (6) 4 ≤ National Institute of Health Stroke Scale (NIHSS) score ≤ 20, (7) first attack or previous history of cerebral infarction but without disability before this attack (modified Rankin Scale [mRS] score ≤1), and (8) signed informed consent.

### Exclusion Criteria

The exclusion criteria will be as follows: (1) accompanied by cerebral hemorrhage tendency, cerebral hemorrhage after cerebral infarction, or had cerebral hemorrhage within 3 months; (2) combined with depression or dementia after stroke, posterior circulation infarct, transient ischemic attack, abnormal intracranial vascular networks, asymptomatic cerebral infarction, or large area of cerebral infarction with unstable vital signs; (3) subject withdrawal of TCM prescriptions for treating IS less than one week, or had used thrombolytic therapy after the onset of the disease; (4) patients with comorbidity or condition that would confound the neurological and functional evaluations; (5) clinical examination suggesting hemiplegia caused by brain tumors, brain trauma, or cerebral parasitic diseases, and cerebral embolism caused by rheumatic heart disease, coronary heart disease, and other heart diseases with atrial fibrillation; (6) patients unable to live independently or unsuitable for efficacy evaluation due to various diseases; (7) other serious cardio/cerebro-vascular, liver, kidney, hematopoietic system diseases and those who have undergone major surgery recently; (8) psychiatric patients, patients with severe depression, alcohol addicts or history of substance abuse; (9) females who are pregnant or lactating or have a positive pregnancy test at time of admission; (10) allergic to research drugs and its ingredients or have severe allergies; (11) participation in other clinical trials in the previous 3 months; or (12) being judged as inappropriate by investigators.

### Recruitment Strategies

We will recruit patients from the outpatient and inpatient populations of Neurology or Encephalology departments in seven centers (**Table 2**). Recruitment strategies will include publishing recruitment advertisements on social media (such as WeChat, QQ, etc., similar to Facebook), online publications, and at community centers. Patients who consent to participate will be examined and diagnosed by an associate chief physician and registered in an online allocation system after the inclusion criteria are confirmed and informed consent is signed.

### Randomization and Blinding

Central randomization will be performed using stratified and permuted blocks. According to the randomized clinical study program, with the help of the SAS 9.4 statistical software package PROC PLAN process, a stratified randomization method will be adopted to list the random coding table and generate the random arrangement of subjects’ treatment. Patients will be randomized in blocks of varying sizes within each center and stratified by centers.

All eligible participants will be randomly divided into the experimental group 1 (BHG group), experimental group 2 (NXTC group), experimental group 3 (YTG group), and placebo control group using a 1:2:1:1 ratio. According to the randomized clinical study program, the randomized code of the trial drug by statistical experts is the unique identification code of participants. Considering that the dosage forms include granules and capsules, a double-blind and double-simulation design will be adopted. All the participants, researchers, research assistants (conducting interviews with the participants), laboratory and inspection staff, and statisticians will be blinded to treatment assignment until the study is completed.

### Unblinding

The patient’s group allocation should be known in the event of adverse events (AEs) and can be obtained from the drug administrators when necessary. Researchers should contact the inspector and report the reasons for unblinding within 24 h. The precise cause of unblinding, the date of AEs, the treatment situation, and the results must be reported in the case report form (CRF) and signed by the administrator.

When the trial is completed, the data will be locked and cannot be changed after verification. Then the unblinding process will be conducted by the researchers, operated by the administrators, and the number of unblinding will be transferred to the sponsors.

### Intervention

The preparation and distribution of intervention drugs will be performed by Buchang Pharmaceutical Co., Ltd. The characteristics of the simulants in terms of packaging, color, shape, and flavor will be similar to those of BHG, NXTC, and YTG. After the treatment, drug packages will be returned to the investigators. Participants will receive the following interventions for 28 days.

***Experimental group 1***: capsule simulants (0.4 g/capsule, op, four capsules/time, thrice daily), BHG (5.5 g/package, op, one pack/time, thrice daily);

***Experimental group 2*:** NXTC (0.4 g/capsule, op, four capsules/time, thrice daily), inert granules (5.5 g/package, op, one pack/time, thrice daily);

***Experimental group 3*:** capsule simulants (0.4 g/capsule, op, four capsules/time, thrice daily), YTG (5.5 g/package, op, one pack/time, thrice daily);

***Placebo control group*:** capsule simulants (0.4 g/capsule, op, four capsules/time, thrice daily), inert granules (5.5 g/package, op, one pack/time, thrice daily).

All the participants will receive basic treatment in accordance with the “Guidelines for diagnosis and treatment of ischemic stroke in China” (Chinese Medical Association, 2015), and the drug and dosage will be formulated by the researchers according to the clinical situation. However, we should pay attention to the following guidelines: (1) only single antiplatelet drug therapy should be given; (2) except for experimental drugs and basic treatment, do not use any other TCM patent medicine or TCM therapy (including acupuncture) during the observation period; and (3) during the observation period, basic therapeutic drugs and other drugs or treatments that must be taken for complicated diseases should be listed in the CRF (e.g., drug name, usage, dosage, time of taking, etc.).

### Outcome Measures

#### Primary Outcome

The primary outcome will be the NIHSS score, which is commonly used to evaluate neurological recovery and quality of life in clinical practice (Yaghi et al., 2016). The NIHSS score will be measured at the end of the 28-day treatment period and compared with baseline, and changes will be compared between groups (**Table 3**).

**Table 3 T3:** Measurement items and time line.

Visit	Screening	Intervention	Follow-up	
	V1	V2	V3	V4
Unit:day	-7-0	28 ± 4	90	180
Screening the subject	×			
Informed consent form	×			
Demographic information	×			
Inclusion/exclusion criteria	×			
Get the random number	×			
Previous medical history and allergy history	×			
Concomitant diseases and treatment history	×			
Connect to the Internet hospital “Doctor Tao” platform	×			
Head CT/MRI	×**^#^**			
Urine pregnancy test (HCG)	×**^*^**			
Vital signs^1^ and physical examination	×	×		
Blood routine^2^	×	×		
Urine routine	×	×		
Liver^3^ and kidney^4^ function	×	×		
Blood coagulation function^5^	×	×		
Fasting glucose	×	×		
12-lead electrocardiogram	×	×		
NIHSS	×	×	×	
TCM symptom score	×	×	×	
mRS score	×	×	×	
Barthel Index	×	×	×	
Biological effect indicators	×	×		
Metabolic and proteome data	×	×		
Pharmacokinetic index	×			
Drug distribution	×			
Recovery drug		×		
Record adverse events		×		×
Record drug combination		×		×
Compliance prediction		×		

^#^if imaging examination shows typical lesions after the onset and 4 weeks prior to the study can be avoided.

^*^Only women of child-bearing age were tested before the trial.

^1^Vital signs including the temperature, heart rate, respiration, blood pressure.

^2^Blood routine tests including red blood cells, hemoglobin, white blood cells, and platelets.

^3^Liver function tests including alanine and aspartate aminotransferases, alkaline phosphatase level, total bilirubin, and gamma-glutamyl transferase.

^4^Kidney function tests including creatinine and blood urea nitrogen.

^5^Blood coagulation function tests including prothrombin time, activated partial thromboplastin time, thrombin time, and fibrinogen.

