#### Secondary Outcomes

The study has three secondary clinical efficacy end-points:

The modified Rankin scale (mRS) will be used to evaluate the subjects’ degree of disability. We will record the ratio in each group with mRS scores 0–5, and the proportion of subjects with mRS ≤1 in each group. Comparisons will be made on day 28 (immediately after treatment) and day 90 after IS onset, and statistical analysis will be conducted between groups.The activity of daily living (ADL) scale will be measured with the Barthel Index (BI). The differences of BI scores (before and 28 days after treatment, and 90 days after onset) will be compared within and between the groups, and the proportion of participants with BI scores ≥90 will be recorded.TCM symptom scores will be used to quantitatively score the symptoms. The differences in TCM symptom scores between groups will be compared for baseline and 28 days after treatment and 90 days after onset, and the differences between groups will be calculated. The comprehensive curative effect criteria are as follows: i) clinically resolved: symptoms and signs disappear or largely decrease, syndrome score decrease by ≥95%; ii) significant effect: symptoms and signs are significantly improved, syndrome score decrease by ≥70%; iii) effective: symptoms and signs are improved, syndrome score reduced by ≥30%; and iv) no effect: no significant improvement or even aggravation of symptoms and signs, <30% reduction of syndrome score (Jin et al., 2019). The formula for evaluation (nimodipine method) is:$$\text{comprehensive curative effect}=\frac{\text{integral before treatment}-\text{integral after treatment}}{\text{integral before treatment}}\times 100\%.$$

The number of total effective cases including clinically resolved cases, significant effect cases, and effective cases (i–iii).

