### Safety and AE Monitoring

In this study, safety will be monitored by clinical research associates including AEs, serious AEs, withdrawals or treatment modification due to AEs, vital signs and physical examinations, routine blood and urine tests, liver and kidney function tests, blood coagulation function test, fasting glucose test, 12-lead electrocardiogram, and concomitant medications for management of AEs. The severity of AEs will be graded using CTCAE version 3.0. The indexes and time points for data collection are shown in **Table 3**.

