### Quality Control of the Intervention

To ensure the quality of this trial, a multicenter trial coordination committee and general director will be tasked with solving related problems. The coordination committee includes the leaders of each center and the head sponsor who will all complete pre-clinical training. All staff including the operators, researchers, physicians, data collectors, and analyzers will fully understand the purpose and content of the trial. This trial will be inspected by the China Food and Drug Administration (CFDA), sponsor, and clinical research organization throughout the process.

The sponsor will appoint inspectors to ensure the rights and interests of the participants and the accuracy and integrity of data. They shall also supervise the implementation, management norms, and relevant regulations of this trial and provide regular on-site supervision. In the monitoring process, if the CRF table does not conform to the protocol, the inspector has the right to propose suggestions for modification. If the CRF table is not standardized (e.g., input errors), researchers are responsible for following the original data for correction. Furthermore, pre-clinical trial training will be provided to ensure that researchers fully understand the protocol and the specific contents of each index. Objective indexes should be tested according to the time points and methods specified in the protocol, and the AEs or unexpected toxic and side effects should be observed and followed up.

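### Table 3 schedules adverse-event and concomitant-drug recording at day 28 and day 180 but not at the day-90 visit, where the later secondary outcomes are measured

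*Protocol article*

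**What the plan says.** Table 3 (Protocol article, Primary Outcome) has four visits: V1 at screening, V2 at day 28 ± 4, V3 at day 90 and V4 at day 180. The rows "Record adverse events" and "Record drug combination" carry a mark at V2 and at V4 and none at V3. NIHSS, TCM symptom score, mRS and Barthel Index are marked at V1, V2 and V3. At V4 the two recording rows are the only ones marked.

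Four other places bear on this:

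- Safety and AE Monitoring lists adverse events, serious adverse events and drugs given to manage them, and leaves timing to the table: "The indexes and time points for data collection are shown in" Table 3.
- Secondary Outcomes, on the mRS: "Comparisons will be made on day 28 (immediately after treatment) and day 90 after IS onset". The Barthel Index and TCM symptom score are also compared at 90 days.
- Intervention bars other Chinese medicine products and therapies during an observation period, and asks that "during the observation period, basic therapeutic drugs and other drugs or treatments that must be taken for complicated diseases should be listed in the CRF", with the time of taking. It does not say when that period ends.
- Quality Control of the Intervention says that "the AEs or unexpected toxic and side effects should be observed and followed up", with no visit or interval attached.

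**The concern.** The sponsor evidently wants adverse-event and drug data from after treatment, since V4 is scheduled for nothing else. Yet the schedule passes over a visit at which the patient is already being assessed, and no reason is given.

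Two things are at stake. The first is safety. An adverse event that begins after V2 has its next scheduled recording at V4, and someone who comes to V3 but not to V4 has none.

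The second is the reading of the day-90 comparisons. If the observation period extends beyond day 28, V3 is where adherence to the ban on other Chinese medicine would naturally be checked. If it ends at day 28, such treatment may begin before the day-90 comparison, and its use in each arm needs to be known. On either reading, drug data tied to V3 help to interpret those outcomes.

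**Working it through.** No sample-size, power or error-rate figure bears on this point, so there is no stated figure to reproduce. The check is a reading of Table 3 and differences of visit days.

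**Step 1: is the blank at V3 real?** Each row has a label and four visit cells.

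| Row | V1 | V2 | V3 | V4 |
|---|---|---|---|---|
| NIHSS | × | × | × | |
| Routine blood tests | × | × | | |
| Adverse events | | × | | × |
| Drug combination | | × | | × |

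The NIHSS row ends at V3 and the blood-test row at V2, as expected. The columns are intact, and the blank at V3 in the last two rows is not a shifted mark.

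**Step 2: length of the gap on the table's day numbers.**

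- V2 to V4: 180 - 28 = 152 days. With the ±4-day window on V2: 180 - 32 = 148 to 180 - 24 = 156 days.

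**Step 3: other time origins.** The table does not say where days 90 and 180 are counted from, and the text points in different directions.

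- The Abstract says "All subjects will undergo 28 days of treatment and then followed for another 180 days". V4 would then fall 28 + 180 = 208 days after the start of treatment, and the gap is 208 - 28 = 180 days. With the window: 208 - 32 = 176 to 208 - 24 = 184 days.
- Secondary Outcomes counts day 90 from stroke onset. Assume that V4 is counted in the same way. Entry requires a "course of disease of 1–4 weeks", so enrolment is 7 to 28 days after onset. The gap is then 180 - 28 - 28 = 124 to 180 - 7 - 28 = 145 days. With the window: 180 - 28 - 32 = 120 to 180 - 7 - 24 = 149 days.

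Across all readings the gap runs from 120 to 184 days.

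**Step 4: effect of recording at V3, on the table's day numbers.**

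- V2 to V3: 90 - 28 = 62 days (58 to 66 with the window).
- V3 to V4: 180 - 90 = 90 days.
- The longest interval falls from 152 to 90 days, a reduction of 1 - 90/152 = 41%.

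**Step 5: what is already covered.** V2 carries both recording rows, vital signs, routine blood and urine tests, liver and kidney function, coagulation, fasting glucose and the ECG. The treatment period and the primary outcome (NIHSS change to day 28) therefore lie before the gap.

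**The case against.** The best case for the plan is that a mark in Table 3 shows when a form is completed, not the only time information is gathered. One mark at V2 covers the whole treatment period, so one mark at V4 could stand for cumulative recording up to day 180. The text asks for drugs to be listed with the time of taking and for adverse events to be followed up, and ties neither to a visit. Dated drug entries completed at V4 could still be placed before or after day 90. Detailed reporting procedures may also sit in the full protocol, and the outcomes concerned are secondary ones in a self-described pilot.

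Much of this limits the point, and three stronger readings should be set aside:

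- A reader might infer that the trial's safety data as a whole rest on patients' memory over five months. The documents do not support that. Treatment-period events, laboratory tests and the ECG are captured at V2, and nothing says that later events are collected by recall.
- A reader might infer that co-treatment around day 90 will be missing altogether. For patients who reach V4 it may be late rather than absent.
- A reader might turn the 20% dropout allowance in Sample Size Estimates (32 of 160) into a share of patients who attend V3 and lack later data. The timing of dropout is not given, so no such share can be derived.

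The objection does not remove the gap. The article itself makes Table 3 the schedule for safety time points, so this is a stated schedule and not a detail left to another document. The general wording on drug listing and adverse-event follow-up supplies no visit, no interval and no end to the observation period.

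**Conclusion.** The point holds in limited form. Table 3 has no adverse-event or concomitant-drug recording at V3, although V3 takes place and supplies the day-90 secondary outcomes. After treatment, neither item has a scheduled recording for 152 days if days run from the start of treatment, and for roughly 120 to 184 days across the possible time origins. The lower end assumes that V4 is counted from stroke onset, which the documents do not state. A patient who attends V3 and is lost before V4 has no scheduled post-treatment recording; how many such patients there will be cannot be estimated from the documents.

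The consequence is weaker capture of post-treatment events and less secure interpretation of the day-90 comparisons. The conclusion takes the table at face value. If recording between V2 and V4 is in fact continuous, the fault is that the article does not say so.

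**What to change.** 1. Mark the adverse-event and drug-combination rows at V3 in Table 3.
2. Reconcile the table with Intervention, Safety and AE Monitoring, and Quality Control of the Intervention: say whether recording between V2 and V4 is continuous or by visit, and state when the observation period ends.
3. State the time origin of days 90 and 180, so that the intervals can be read without assumption.
4. Summarise co-treatment between V2 and V3 by arm, including other Chinese medicine, beside the day-90 outcomes.

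The cost is two extra CRF items at a visit already scheduled, plus one descriptive table. No new visit or test is needed, and the primary analysis is unchanged.
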